### Statistical analysis

Baseline and follow-up primary outcomes data will be analysed using a logistic mixed model to detect change over time in the reported receipt of recommended antenatal care for addressing alcohol consumption during pregnancy. For the secondary trial outcome, linear mixed models will be used to analyse changes in AUDIT-C scores of participants between baselines and follow up periods. The models will have a period term (fixed effect, reflecting pre-post difference, the main indicator of effect) and health sector term (fixed effect). Where appropriate, the models will also include fixed effects for client group (booking in, 27–28 weeks gestation, 35–36 weeks gestation) and a time term (fixed effect, to pick up any secular trend). In the latter models, a client group by period term will detect differences between the client groups in their response to the intervention. Where the interaction terms are significant, subgroup analyses will be reported for each of the three client groups. Descriptive statistics will be used to report on process measures and interventions costs. Process outcomes will be used to narratively interpret the results of primary outcome analysis. SAS (V9.3 or later) will be used for all statistical analyses.

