#### Process evaluation measures

The acceptability, appropriateness, feasibility, intervention fidelity and reach of the model of care for addressing maternal alcohol consumption in pregnancy and the implementation strategies will be assessed via surveys of women and clinicians and project records. These process measures will be based on an implementation evaluation framework [61] and use validated measures where available [62]. Measures to assess implementation intervention reach will include participation of antenatal clinical staff in educational meetings, interaction with local opinion leaders, involvement in academic detailing/ audit and feedback sessions, and receipts of clinical practice guidelines. To determine reach of the implementation intervention strategies across different groups of clinicians, data will be collected from clinicians on position/profession, level of training, and length of time working in current antenatal service and in antenatal services generally. To assess delivery of the model of care across different demographic groups of women, the following information will be collected from pregnant women: age, gender, highest level of education, employment status, geographical location, Aboriginal or Torres Strait Islander status of woman and baby, household composition, current gestation, gestation at first antenatal clinic visit, whether attending care for first or subsequent pregnancy and alcohol consumption prior pregnancy (via AUDIT-C).

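### The stated AUDIT-C model adjusts for no characteristic of the woman, so case mix is only partly corrected and some precision is given up

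*Protocol article*

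**What the plan says.** The secondary outcome is the total AUDIT-C score since the woman knew she was pregnant, by self-report (Secondary trial outcome). In Statistical analysis the method is that "linear mixed models will be used to analyse changes in AUDIT-C scores of participants between baselines and follow up periods".

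The terms follow in the same section: "The models will have a period term (fixed effect, reflecting pre-post difference, the main indicator of effect) and health sector term (fixed effect". Two more are conditional: "Where appropriate, the models will also include fixed effects for client group", and, under the same condition, "a time term (fixed effect, to pick up any secular trend". A client group by period interaction completes the list. None of these terms describes the individual woman, apart from the visit at which she was sampled.

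Under Process evaluation measures, the women's survey is said to collect "age, gender, highest level of education, employment status, geographical location, Aboriginal or Torres Strait Islander status of woman and baby, household composition, current gestation", and further on "whether attending care for first or subsequent pregnancy and alcohol consumption prior pregnancy (via AUDIT-C". The purpose given is this: "To assess delivery of the model of care across different demographic groups of women, the following information will be collected from pregnant women".

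Study design and setting describes repeated cross-sections in three sectors, with the outcome judged by comparing baseline with follow-up across the sectors combined.

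**The concern.** The women surveyed at baseline and at follow-up are different people. Randomising the order of only three sectors does not balance the women sampled before and after each step. If the mix of respondents changes between phases, and the changed characteristic predicts drinking, part of that change is read as an effect on AUDIT-C.

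The article describes routes by which respondents could change when a sector's intervention starts:

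- Women can be excluded from the survey at clinical discretion, and clinicians know when their service is in its intervention period.
- Women can opt out during the clinic visit, where the new alcohol assessment is to be delivered.
- About 30% of invited women are expected not to take part.

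These are possibilities; nothing in the article shows that they occur. A change of this kind would be tied to each sector's own start date, so sector, client group and a time term common to all sectors would not remove it.

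Precision is also at stake. The power calculation covers only the primary outcomes, and predictors of drinking that are already collected would reduce the residual variance at almost no cost.

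**Working it through.** The article gives no sample size, power, standard deviation or effect for AUDIT-C, so there is no figure of its own to reproduce. Everything below is in units of the AUDIT-C standard deviation.

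**Inputs from the article**
- 200 women per month over three sectors, so 200/3 = 66.7 per sector-month (equal split assumed).
- Baseline of 7, 13 and 19 months: 7 months before the first sector starts, then six-month steps.
- A 7-month intervention in each sector, and 34 months in all. Follow-up is therefore 34 - 14 = 20, 34 - 20 = 14 and 34 - 26 = 8 months.

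**Assumptions**
- R², the share of variance explained by the covariates.
- r, the correlation of a predictor with the outcome.
- d, the shift in that predictor between phases, in SDs.
- The share of variance lying between sector-months: 0 or 1%. The 0.01 intra-class correlation in the article belongs to the primary-outcome calculation.

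**1. Standard error of the period effect, with period and sector only**

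Each sector with b baseline and f follow-up months contributes 66.7 × bf/(b + f):
- 7 × 20/27 = 5.185
- 13 × 14/27 = 6.741
- 19 × 8/27 = 5.630

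The sum is 17.556, and 17.556 × 66.7 = 1,170. SE = 1/√1,170 = 0.029 SD. The follow-up rule taken literally ends the study at month 33, which gives 0.030. Weighted least squares on the sector-month means gives 0.067 with a linear time term. With 1% of variance between sector-months and no time term, it gives 0.038.

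**2. Precision gained by adjustment**

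With no sector-month variance the SE multiplier is √(1 - R²). With 1% between sector-months it is √{[0.99(1 - R²)/66.7 + 0.01] / [0.99/66.7 + 0.01]}, where the denominator is 0.01485 + 0.01 = 0.02485.

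| R² (assumed) | Multiplier, none between sector-months | Multiplier, 1% between sector-months |
|---|---|---|
| 0.1 | 0.949 | 0.970 |
| 0.2 | 0.894 | √(0.02188/0.02485) = 0.938 |
| 0.3 | 0.837 | 0.906 |
| 0.4 | 0.775 | √(0.01891/0.02485) = 0.872 |

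For R² of 0.2 to 0.4 the SE falls 11-23% in the first case and about 6-13% in the second.

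**3. Bias from a shift in respondents that coincides with the intervention**

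Bias = r × d. The chance of a false positive at two-sided 5% is 1 - Φ(1.96 - bias/SE) + Φ(-1.96 - bias/SE).

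- r = 0.2, d = 0.05: bias 0.010 SD. With SE 0.029 the false-positive rate is about 6%.
- r = 0.4, d = 0.1: bias 0.040 SD. With SE 0.029 it is about 28%; with SE 0.038, about 19%; with linear time and SE 0.067, about 9%.

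A time term lowers the false-positive rate in the second case by widening the SE. The bias itself stays, because this shift is not common to all sectors. Adjustment removes only the part of a shift that the chosen covariates carry.

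**The case against.** The case on the other side has real force.

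- **The article is a summary.** It does not say that its list of terms is complete, and an adjusted analysis may stand in an analysis plan that is not shown. Leaving covariates out is not an error in itself. A reader might infer that the demographic items serve process evaluation alone, but the article gives that purpose without saying it is the only one.
- **Case mix is partly handled.** A reader might infer that change between phases goes uncorrected. The article does not support that: sector is always fitted, client group may be, and a time term would absorb smooth drift common to all sectors. Staggered steps also give overlapping calendar time, women are sampled at random each week, the same survey procedures are described for the whole study, and survey staff are blind to the step order.
- **The sizes are assumed.** No AUDIT-C standard deviation, correlation or case-mix shift is given. Whether time is fitted changes the SE more (0.067/0.029, about 2.3-fold) than any covariate considered here.
- **Pre-pregnancy AUDIT-C is not a clean baseline.** A reader might want it in the main model, as the same scale measured before pregnancy. But it is recalled in a survey after the appointment, and at follow-up that appointment is meant to include AUDIT-C questions and advice on harm. Recall or disclosure could differ by phase, so adjusting for it could create or hide an effect.

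All four points stand and limit the claim. They do not reach age, education, first or later pregnancy, or Aboriginal or Torres Strait Islander status. The intervention cannot change these, and they are already collected. The article also does more than stay silent: it lists the model's terms, and that choice is open to comment.

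**Conclusion.** The point holds as an improvement to the secondary-outcome analysis. The stated AUDIT-C model has no woman-level covariate, although its effect is a before-and-after comparison of different women in three sectors. Case mix is only partly corrected, and some precision is given up.

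The size cannot be established from the article. An SE reduction of 11-23%, or about 6-13% with 1% of variance between sector-months, rests on an assumed R² of 20-40%. The demographic items alone may explain less; at 10% the reductions are about 5% and 3%. The bias ranges from negligible to serious with the assumed shift and correlation. The article gives no evidence that such a shift will occur, so the planned result should not be called biased.

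The point is confined to the AUDIT-C model. Nothing here shows a fault in the logistic models for the primary outcomes.

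**What to change.** Before outcome data are examined, add to the plan for the secondary outcome:

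- An AUDIT-C linear mixed model with age, education, first versus later pregnancy, and Aboriginal or Torres Strait Islander status as fixed covariates, alongside the terms already listed.
- The model without these covariates, reported beside it.
- A sensitivity analysis that adds pre-pregnancy AUDIT-C, with a sentence saying that it is recalled after the appointment and that its reporting could differ by phase.

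The cost is analysis wording and a little extra analysis. The survey already collects every item, so no new data are needed.

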## Methods

### Study design and setting

The study will be a randomised stepped-wedge controlled trial design conducted in three sectors (clusters) in the Hunter New England Local Health District in New South Wales, Australia. The sectors are geographically defined groupings of antenatal facilities with common operational management. As shown in Fig. 1, repeated cross-sectional outcome data will be gathered on a weekly basis across all three sectors for the duration of the study (34 months). Baseline (current practice/control phase) data will be collected for each of the three sectors from 7 months prior to the commencement of the intervention in the first sector to the start of the intervention in each sector. Stepped implementation of a 7-month practice change intervention will be delivered in a randomly selected order at six monthly intervals. Follow-up data will continue to be collected for all three sectors 7 months following completion of the practice change intervention in the third sector. The outcomes of the trial will be determined by comparing practice change outcomes between the baseline and follow up periods for the three sectors combined.

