##### Implementation intervention delivery timeline

The intervention strategies listed above will be implemented in each sector for 7 months prior to follow up data collection (Fig. 1). This will include a 1-month period introducing the practice change and a 6-month intensive practice change intervention. Given their organisational and system focus, all strategies, other than the local opinion leader (Clinical Midwife Educator (CME)) and academic detailing strategies, have the potential to continue to be implemented following the 7-month study intervention period, subject to the operational decisions of the Local Health District.

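### A single constant period effect, fitted with a time term over unequal follow-up of about 19, 13 and 7 months, is biased in either direction if the effect changes after the intervention ends

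*Protocol article*

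**What the plan says.** Under Study design and setting, the target is set as "comparing practice change outcomes between the baseline and follow up periods for the three sectors combined". Baseline runs "from 7 months prior to the commencement of the intervention in the first sector to the start of the intervention in each sector". The steps are described as "Stepped implementation of a 7-month practice change intervention will be delivered in a randomly selected order at six monthly intervals", and the end of data collection as "Follow-up data will continue to be collected for all three sectors 7 months following completion of the practice change intervention in the third sector".

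Under Implementation intervention delivery timeline, follow-up comes after the 7-month intervention, and "all strategies, other than the local opinion leader (Clinical Midwife Educator (CME)) and academic detailing strategies, have the potential to continue", subject to decisions of the health district. Table 1 (strategy 4) gives the educator the task of delivering and monitoring every support strategy.

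Under Statistical analysis, "Baseline and follow-up primary outcomes data will be analysed using a logistic mixed model". The effect is carried by a "period term (fixed effect, reflecting pre-post difference, the main indicator of effect", with a fixed sector term. Where appropriate, the model also has client group and "a time term (fixed effect, to pick up any secular trend". The only interaction named is client group by period. No term lets the effect vary with time since the intervention.

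**The concern.** One period term assumes the same effect in every follow-up month of every sector. The plan's own timeline gives reason to doubt this: the educator and academic detailing end just as follow-up begins, and the remaining strategies may or may not continue.

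Unequal follow-up makes the assumption matter. In the last seven calendar months all three sectors are in follow-up, but sector 1 is in its months 13 to 19, sector 2 in its months 7 to 13 and sector 3 in its months 1 to 7. A time-adjusted model treats sector 1 as a stable comparator for sector 3. If the effect in sector 1 has fallen since its early follow-up, the model reads the fall as calendar time and adds it to the gain credited to sector 3. If the effect in sector 1 has grown, the gain is understated. A fading intervention could then score higher than one that lasts.

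**Working it through.** **Timeline.** Baseline is 7, 7+6 = 13 and 7+12 = 19 months. Each intervention lasts 7 months. Follow-up ends at 7+12+7+7 = 33 months, so it lasts 33−14 = 19, 33−20 = 13 and 33−26 = 7 months. The article states 34 months in total, one more than the parts sum to. That would give 20, 14 and 8 months and does not change the direction of the results.

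**The plan's own figure.** The sample size section gives 200 women per month (72 × 0.70 ≈ 50 per week; 50 × 48/12 = 200), a baseline of 50%, a 15-point increase, a 1.25% threshold and 80% power. The power model is not stated. I took fixed sector effects, monthly time effects, 200/3 = 66.7 women per sector-month, variance 0.25, a two-sided test and baseline and follow-up months only:

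- SE = √(0.25/66.7 × [(X′X)⁻¹] for the period term) = 0.0441
- Power = Φ(0.15/0.0441 − 2.498) = 81.8%

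This is close to the stated 80%, so the layout is a fair basis. A random sector effect with the stated ICC of 0.01 gives 82.6%. Linear time gives SE 0.0344 and 96.8%.

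**Weights of the single term.** Model: E[y] = sector + time + θ × period. The least-squares estimate of θ is a weighted sum of the sector-month results. Its expected value is the sum of each follow-up month's weight times the true effect in that month.

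| Time term | Follow-up months 1–7 | 8–13 | 14–19 |
|---|---|---|---|
| none | 0.63 | 0.28 | 0.10 |
| linear | 1.44 | −0.03 | −0.40 |
| monthly | 1.56 | −0.21 | −0.35 |

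The weights sum to 1 apart from rounding, so a constant effect of 15 is returned as 15.0.

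**Assumed curves.** The article gives no figure for change over follow-up. The true mean is taken over the 19+13+7 = 39 observed sector-months, of which 3 × 7 = 21 lie in months 1–7 and 18 are later.

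- Drop from 15 to 5 after month 7. True mean (21×15 + 18×5)/39 = 10.4. Linear time: 1.44×15 − 0.44×5 = 19.4. Monthly time: 1.56×15 − 0.56×5 = 20.6.
- Drop from 15 to 10. True mean (21×15 + 18×10)/39 = 12.7. Estimates 1.44×15 − 0.44×10 = 17.2 and 1.56×15 − 0.56×10 = 17.8.
- Gradual fall from 15 to 5 over 12 months, then flat. True mean 9.7; estimates 17.0 and 17.3.
- Linear growth from 7.5 in the first to 15 in the 19th follow-up month. True mean 10.4; estimate 5.8 with either time form.

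With no time term the same four cases give 11.3, 13.1, 10.3 and 10.0, each within 1 point of its true mean.

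**Scale check.** These figures are risk differences, whereas the plan's model is logistic. A logistic fit to a linear fall from 15 points to 0 by month 19 gives odds ratios of 2.07 (linear) and 2.08 (monthly), against a true mean of 1.36 and an initial value of (0.65/0.35)/(0.5/0.5) = 1.86. The direction is the same.

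**Split model.** The period term is replaced by one term for follow-up months 1–7 and one for later months.

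- Drop at month 7: both parts are recovered exactly.
- Gradual fall: months 1–7 give 14.7 (linear) or 14.5 (monthly) against 12.5; later months give 9.6 or 9.5 against 6.4.
- Precision for months 1–7: monthly time, SE 0.0469, power Φ(0.15/0.0469 − 2.498) = 75.7%; linear time, SE 0.0361, power 95.2%.

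**The case against.** The strongest reply is that a constant-effect term is the conventional stepped-wedge model, that the core model here is period plus sector, and that time enters only where appropriate. Without time the error is small. This stands and limits the point to the time-adjusted analysis. It does not remove it, because the article justifies the design partly by its capacity to identify secular trends, and dropping time would leave any such trend in the estimate.

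Second, no document says the effect will wane. Prompts, guidelines and performance measures are structural and may continue. This also stands. A reader might infer that the plan overstates the effect; the documents support only that it can err in either direction if the effect changes.

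Third, a reader might infer that the cost-effectiveness ratio carries the same error. The article divides by the difference in the primary outcome and does not say that this is the model coefficient, so the link is not established.

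Fourth, making the first 7 months the primary contrast would change the target set under Study design and setting and would cost power. That is fair, so the split belongs beside the planned result. Finally, exposure-time analyses are often left to an analysis plan, which is not shown here. The point therefore concerns what the article does fix: one term, named as the main indicator of effect.

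**Conclusion.** The point holds in conditional form. If the effect changes with time since the intervention and the time term is fitted, the single term is not an average follow-up effect. In the waning examples it exceeds even the largest true effect at any time. An effect that collapses from 15 to 5 is reported as about 20, while one that stays at 15 is reported as 15. In the growth example it falls below the smallest true effect (5.8 against 7.5).

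The unequal follow-up and the end of the educator and academic-detailing strategies come from the article. The sizes of change are assumptions, and the magnitudes rest on a 33-month layout with intervention months left out and equal monthly samples per sector. If the effect is constant, or time is not fitted, there is no material problem of this kind.

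**What to change.** Keep the planned single-term result. Beside it, pre-specify a time-adjusted model with separate terms for the first 7 months after the intervention (observed in all three sectors) and for later follow-up. Report both estimates. State that if they differ, the single term will not be read as the average follow-up effect. Check any cost-effectiveness ratio that uses the model estimate against the split.

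This needs no new data. On baseline and follow-up data, power for 15 points in the first-7-month contrast is about 76% instead of 82% with monthly time, which is below the planned 80%, or 95% instead of 97% with linear time. The split is not a complete cure: under the gradual fall it is still about 2 points too high for months 1–7 and about 3 points too high for later months. The later estimate should therefore be read with caution as evidence of sustained effect.

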**Fig. 1 Fig1:**

Study design. Figure 1 shows the trial design and implementation of the trial data collection and intervention components over the course of the 34 months trial period. Repeated cross-sectional outcome data from surveys of pregnant women will be gathered on a weekly basis across all three sectors for the duration of the study. Baseline data will be collected for each of the three sectors from 7 months prior to the commencement of the intervention in the first sector to the start of the intervention in each sector. Stepped implementation of a 7-month practice change intervention will be delivered in a randomly selected order at six monthly intervals. Follow-up data will continue to be collected for all three sectors 7 months following completion of the practice change intervention in the third sector

A randomised stepped-wedge controlled trial design is recommended for the evaluation of complex practice change interventions in settings such as health services as it provides a number of pragmatic and scientific advantages over a randomised controlled trial design [48, 49]. First, it provides a similar level of evidence as a standard parallel cluster randomised controlled trial (RCT) [50]. Second, although all participants will receive the intervention, its sequential implementation across three sectors provides the capacity to identify secular trends, i.e. changes over time before the intervention is implemented [48]. Third, the design addresses the practical difficulty of recruiting the number of similar antenatal services that would be required for a parallel cluster RCT, instead allowing each cluster to act as its own control [48, 49]. Finally, the design provides an opportunity for all participating services and women to receive the intervention, overcoming ethical and logistical challenges arising from withholding the intervention [50].

Public antenatal services are the largest provider of antenatal health care in Australia, providing services to a diverse population [51]. The antenatal services in the three sectors service urban and rural areas and provide care to over 6000 women annually, accounting for approximately 70% of births in Hunter New England Local Health District public hospitals [52].

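### Calendar time enters the primary model only under an undefined condition; if it is left out, steady secular drift is counted as intervention effect

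*Protocol article*

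**What the plan says.** The Statistical analysis section states which terms are always present: "The models will have a period term (fixed effect, reflecting pre-post difference, the main indicator of effect) and health sector term (fixed effect"). The next sentence adds further terms under a condition: "Where appropriate, the models will also include fixed effects for client group", followed in the same sentence by the list of client groups, "and a time term (fixed effect, to pick up any secular trend"). The condition therefore governs the time term. No criterion for it is given, and the form of time (linear or categorical) is not stated.

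Under Study design and setting, the trial's outcome is to be determined by "comparing practice change outcomes between the baseline and follow up periods for the three sectors combined". The same section, in the text after the Fig. 1 caption, supports the stepped wedge partly because "its sequential implementation across three sectors provides the capacity to identify secular trends". No sentence in the article makes adjustment for calendar time a fixed part of the primary analysis.

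**The concern.** Within each sector all baseline data precede all follow-up data. Exposure and calendar time are therefore confounded unless time is in the model and the staggered starts are used to separate them. With sector fixed and time absent, each sector is compared only with its own past. The random ordering then contributes nothing to the estimate, and the analysis has the protection of an uncontrolled before-after study.

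The study runs for nearly three years, and the Usual care section says that no sector-wide guideline governs this care. A stable background rate cannot be taken for granted. The unadjusted standard error is small, so even slow drift could give a significant result on any of the four primary outcomes.

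**Working it through.** **Inputs from the article.** Three sectors; 7 months of baseline before the first start; starts six months apart; 7-month intervention; stated duration 34 months; 200 women per month; baseline rate 50%; target +15 points; ICC 0.01; threshold 1.25%.

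**Assumptions.** Equal split between sectors (200/3 = 66.7 women per sector-month); two-sided test (critical value 2.498); intervention months excluded; least squares on the probability scale as an approximation to the logistic model; variance 0.25 per response (p = 0.5). The ICC of 0.01 is applied as a sector-month correlation, with zero correlation as the other end of the range. Drift sizes are assumed, because the article gives none.

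**The plan's own figure.** 72 × 0.70 × 48/12 = 201.6 women per month, against 200 stated. For power, take 7 months of baseline against 7 months of follow-up:
- 1400 women per phase, 467 per sector
- design effect 1 + (467 − 1) × 0.01 = 5.66
- effective n 1400/5.66 = 247 per phase
- power for 50% against 65% at 1.25%: 81.3%, against 80% stated.

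The article does not name its formula, so this matches one plausible variant only. Using the whole phases gives about 85%. Neither calculation contains a time term.

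**Calendar gap.** Starts fall at months 7, 13 and 19, and follow-up begins at months 14, 20 and 26. The components sum to 7 + 2 × 6 + 7 + 7 = 33 months against the stated 34, so both are shown; the difference does not matter here.

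| Sector (in order of start) | Mid-baseline | Mid-follow-up (33 / 34 months) | Gap |
|---|---|---|---|
| First | 3.5 | 23.5 / 24 | 20 / 20.5 |
| Second | 6.5 | 26.5 / 27 | 20 / 20.5 |
| Third | 9.5 | 29.5 / 30 | 20 / 20.5 |

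The gap is the same in every sector, so the weighting is irrelevant: bias = 20 to 20.5 × monthly trend. A drift of 15/20.5 = 0.73 to 15/20 = 0.75 points per month would produce the whole 15-point target.

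**Standard error without time.** Variance = cell variance / Σ[b × f/(b + f)], where b and f are baseline and follow-up months in a sector.
- 34 months: 7×20/27 + 13×14/27 + 19×8/27 = 17.56
- 33 months: 7×19/26 + 13×13/26 + 19×7/26 = 16.73
- Cell variance: 0.25/66.7 = 0.00375 (correlation 0), or 0.00375 + 0.01 × 0.25 = 0.00625 (correlation 0.01)
- SE: 1.46–1.50 points (correlation 0); 1.89–1.93 points (correlation 0.01)

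**Type I error with no true effect**, P(|Z + bias/SE| > 2.498):

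| Assumed drift (points/month) | Spurious effect (points) | Correlation 0 | Correlation 0.01 |
|---|---|---|---|
| 0.1 | 2.0–2.05 | 12–14% | 7–8% |
| 0.2 | 4.0–4.1 | 57–62% | 33–37% |
| 0.25 | 5.0–5.1 | 80–84% | 54–59% |

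A variance of 0.2444 (p = 0.575, midway between 50% and 65%) moves these by about one point.

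**With time in the model.** A linear trend common to the sectors gives zero bias under linear or monthly time. Five step periods cut at months 7, 13, 19 and 26 leave about 0.6 × the monthly trend. Detectable difference = SE × (2.498 + 0.842):

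| Time term | Detectable difference at 80% power, correlation 0 / 0.01 (points) | Power for 15 points, correlation 0 / 0.01 |
|---|---|---|
| None | 5 / 6.3–6.5 | about 100% / about 100% |
| Linear | 11.2–11.5 / 14.5–14.8 | 97–98% / 81–83% |
| Step periods | about 14 / about 18 | 85% / 59–60% |
| Monthly | 14.6–14.7 / about 19 | 82% / 56% |

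The loss is large because, without the intervention months, baseline and follow-up coexist only in months 14 to 19 (first sector against third).

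**The case against.** The article does provide a time term, and for exactly this purpose. The sentence on the client-group-by-period test builds on the fuller models, so they are evidently meant to be fitted. A reader might infer that the trial's default analysis omits time. The text names no default; it supports only that time is optional without a rule. A reader might also infer that time will be kept only if significant, with a further loss of error control. Nothing says so, and the condition could equally concern estimability.

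Three more limits stand. It would be too broad to say that any secular trend passes into the estimate: the result is exact for steady drift, and seasonal or transient patterns may partly cancel. The higher type I figures assume independent responses, whereas the article states an ICC of 0.01, so the lower range deserves equal weight. And the Study design and setting sentence about the three sectors combined describes the contrast; a time-adjusted period term still estimates it, so that sentence does not itself exclude adjustment.

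An unseen analysis plan might define the condition. That does not dispose of the point: the article states the model itself and makes the term that separates time from intervention conditional.

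**Conclusion.** The point holds in this form: the plan permits a primary analysis without calendar time and gives no rule for when time is included. That analysis would ignore the randomised order and pass steady drift into the effect at about 20 times the monthly trend, against the article's own rationale for the design. At an assumed 0.2 points per month (2.4 points a year), the nominal 1.25% error becomes about 33–37% to 57–62%, depending on the correlation assumed. The size of the bias rests on the stated timeline; the error rates rest also on assumed drifts, an equal split between sectors and a linear approximation. The documents do not show that time will be left out or that drift will occur. Because all four primary conclusions rest on this model, the condition should be removed before analysis.

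**What to change.** In the Statistical analysis section, lift the time term out of the conditional sentence. State that every primary and secondary model includes period, health sector and calendar time as fixed effects, and that the intervention effect is the period coefficient from that model. Client group may stay conditional. Prespecify the form of time: for example linear as primary with categorical as a sensitivity analysis, or the reverse. Linear time keeps more precision but relies on a linear trend common to the sectors; categorical time drops the linearity assumption at a cost in power.

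The price is more than one sentence. The 80% power statement under Sample size and power calculations must be restated for the time-adjusted model. At a sector-month correlation of 0.01, linear time still gives about 81–83% power for 15 points, but step or monthly categorical time gives only about 56–60%. The Study design and setting sentence on the three sectors combined needs no change.
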